### Procedures

#### Phase 1: AMT Development

Using an iKT approach, the multidisciplinary research team will consult with police practitioners to tailor AMT content (ie, graphics and recruitment materials) and promote participation and adherence to the AMT intervention by advising on procedural aspects of the research study (ie, feasibility, accessibility, understandability, and relevance). The AMT intervention is comprised of 2 components—HRVBF training and meta-cognitive coping skills.

#### HRVBF Training

Based on an established and publicly available protocol [30], HRVBF has shown significant efficacy in treating a wide variety of disorders, including general anxiety disorder [44-46], major depressive disorder [47-51], hypertension [52-54], asthma [29,55,56], pain [57-61], and posttraumatic stress disorder (PTSD) [62]. Recent meta-analyses revealed a large effect size for HRVBF on reducing symptoms of self-reported anxiety and stress [63] and a moderate effect for HRVBF and paced breathing across targeted physical symptoms and measures of functioning [64]. The original protocol is intended for in-person delivery, and this project will test the effectiveness of web-based HRVBF delivery among police officers. Therefore, the protocol will be formatted for web-based delivery and presented on an LMS using a commercially available HRVBF app paired with a wearable HR monitor.

#### Meta-cognitive Coping Skills

Integrated with HRVBF training, psychoeducational modules will be developed to help individuals cultivate meta-cognitive coping skills, defined as the awareness and understanding of one’s own thought processes and learning how to manage the assessment of one’s own experiences, correctly identify demands and resources, and regulate the appraisal of experiences using attentional and cognitive techniques [2]. Participants will also receive training on developing effective coping skills, including the ability to garner social support from family or friends, engage in positive relationships, and seek professional help when needed. Further, participants will receive training on emotion regulation, such as directing thoughts in the service of reducing demands or increasing resources, the ability to express emotions appropriately and keep them in perspective, and the ability to stay aware of policy and procedures under stress. These meta-cognitive coping skills are rooted in cognitive behavioral therapy principles that have been tested digitally [2] and will be developed in consultation with licensed psychiatrists and clinical coinvestigators (NA).

Research ethics approvals, data sharing agreements with partner institutions, and the procurement of equipment to record HRV and HRVBF will also be finalized during this phase of the study.

#### Phase 2: Testing the Efficacy of the AMT Intervention

##### Overview

The ention assessment, 6 weeks of AMT sessions, and a postintervention assessment. Once participants are deemed eligible for the study, they will be issued a unique deidentified username to access the web-based study, which will be hosted on secure LMS and survey platforms (eg, Qualtrics).

##### Session 1: Preintervention Assessment (1.5 Hours)

During this session participants will complete self-reported baseline measures of: (1) PTSI, including the Personal Health Questionnaire (PHQ-8) for major depressive disorder, General Anxiety Disorder Scale (GAD-7), Depression, Anxiety, and Stress Scale (DASS-42), PTSD checklist (PCL-5), Alcohol Use Disorder Identification Test (AUDIT), Perceived Stress Scale (PSS), and Personal Burnout Subscale of the Copenhagen Burnout Inventory (CBI) [65-71]; (2) resilience and well-being using the Brief Coping Orientation to Problems Experienced Inventory (Brief-COPE), Resilience Scale for Adults (RSA-33), Brief Resilience Scale (BRS), White Bear Suppression Inventory (WBSI), Perseverative Thinking Questionnaire (PTQ), Ultra Brief-Penn State Worry Questionnaire (UB-PSWQ), and Ultra Brief-Rumination Response Styles (UB-RRS) Questionnaire [72-78]; (3) functional wellness and occupational stress using the Sheehan Disability Scale (SDS), Good Health Practices Scale (GHPS), COVID-19 adapted version of the Holmes Rahe Stress Inventory (COVID-19 HRSI), World Health Organization Disability Assessment Scale (WHODAS 2.0) [79-82], operational and organizational subscales of the Police Stress Questionnaire (PSQ) [83], and Lam Employment Absence and Productivity Scale (LEAPS) [84]; and (4) sex and gender-relevant data using the Workplace Gender Discrimination Scale (WGDS) and Gender Experiences Questionnaire (GEQ) [85,86]. Global ratings of stress will be asked at the beginning of each AMT session using a sliding visual analog scale of 0 (not at all stressful) to 10 (extremely stressful) in response to 2 questions: “How stressful was this past week?” and “How stressed are you right now?.” Data will be immediately tabulated to randomly assign participants matched on demographic and outcome variables to either the experimental AMT intervention group that will continue with sessions 2-8 of the protocol or to the waitlist control group that will only be responsible for the first part of session 2 and all of session 8 (postintervention assessment).

Upon completion of session 1, participants will be asked if they want to continue in the study. This secondary “reconsent” is designed to conserve shipment of expensive study equipment (approximately USD $550 total) and retain eligible participants that demonstrate commitment to adhering to the study protocol. If participants agree to continue, they will receive a notification in their personal email confirming their mailing address and will be shipped necessary study materials, including compensation for completing session 1, a wearable HR monitor and chest band, a device equipped with the HRVBF app (an iPad), and a prepaid envelope to return all equipment at the end of the study. Once participants confirm receipt of their equipment in the mail, they will gain access to session 2.

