##### Session 2: Baseline Physiological Assessment and Introduction to AMT (40-60 Minutes)

All participants will be taught via web-based video modules how to apply the wearable HR monitor and configure the HRVBF app. The wearable HR monitor will automatically record date and time-stamped physiological data upon contact with the skin via the chest band and will communicate with the HRVBF app via Bluetooth. All HRV data will be stored locally on the HRVBF app and study device, which will be mailed back to the research team at the end of the study period. In the first part of this session, both experimental and control participants will provide baseline resting HRV and RSA data that will be recorded while participants engage in a 7-minute neutral activity (eg, listening to prerecorded sounds) that does not stimulate arousal or relaxation ([name], unpublished data, 2019). To assess recovery from an acute stressor, participants will perform web-based versions of the Paced Auditory Serial Addition Test (PASAT) [87] and the emotional Stroop task [88], both of which have been shown to induce significant sympathetic arousal but do not simulate traumatic material [28].

Following these baseline physiological assessments, participants in the experimental group will continue with the rest of their session (15-20 min) and begin the AMT intervention. Participants in the control group will not have any programming until session 8 (postintervention assessment).

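### Assignment is made from session 1 data, so equipment receipt, the whole H4-H6 physiological baseline and apparently the reconsent step fall after allocation

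*Protocol article*

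**What the plan says.** The Session 1 section of the protocol article describes the questionnaires and then the allocation: "Data will be immediately tabulated to randomly assign participants matched on demographic and outcome variables". The same sentence gives the arms different duties from there on. The AMT arm does sessions 2 to 8; the waitlist arm does only the opening part of session 2 and then session 8.

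The next paragraph introduces a second consent: "Upon completion of session 1, participants will be asked if they want to continue in the study". One stated purpose is to save on shipping costly equipment. The other is to "retain eligible participants that demonstrate commitment to adhering to the study protocol". Equipment goes to those who agree, and then "Once participants confirm receipt of their equipment in the mail, they will gain access to session 2".

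In the Session 2 section, "both experimental and control participants will provide baseline resting HRV and RSA data", and the PASAT and emotional Stroop tasks supply the baseline for acute stress recovery. Then: "Following these baseline physiological assessments, participants in the experimental group will continue with the rest of their session". The arms are thus already named when the physiological baseline is taken.

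Data Security and Analyses tests H4 to H6 by pre-post repeated measures ANCOVA. The listed covariates are sex, gender, age, years of service and region. The Abstract and the Design section call the trial cluster randomised, although the Session 1 text assigns participants.

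**The concern.** A filter for commitment does no harm to internal validity when it acts before randomisation; it only narrows the population to which the result applies. After randomisation it can remove different kinds of people from the two arms, because one arm faces weekly sessions and twice-daily practice and the other faces a wait. Equipment receipt is a second point of loss of the same kind.

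For H4 to H6 there is more at stake. A person lost before session 2 has no physiological measurement at all and cannot enter a pre-post analysis. The baseline recording is also made remotely by the participant, so knowing one's arm could influence it. For H1 and H2 the questionnaire baseline is taken before assignment, so those hypotheses are exposed only through later losses.

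**Working it through.** **1. Order of steps as written**

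| Step | Section | Relative to assignment |
|---|---|---|
| Questionnaires (H1-H2 baseline) | Session 1 | before: explicit |
| Assignment from tabulated data | Session 1 | – |
| Reconsent | Session 1, following paragraph | after: by text order only |
| Shipping and confirmed receipt | Session 1, following paragraph | after: session 2 opens only once receipt is confirmed |
| Resting HRV, RSA, PASAT and Stroop (H4-H6 baseline) | Session 2, first part | after: arms already named |
| AMT content begins, AMT arm only | Session 2, remainder | after |

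No section moves assignment to a later point. None says when the arm is disclosed.

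**2. The plan's own figure.** Inputs from Recruitment: f = 0.25, alpha 0.05, power 0.80, two groups, two measures, minimum total 128. For two equal groups d = 2f = 0.5. With a noncentral F test, lambda = N × f² = 128 × 0.0625 = 8.0 on 1 and 126 df, power is 0.801. So 128 reproduces under this convention.

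**3. Power after losses.** Loss rates are assumptions, since the article gives none. From 250 allocated, 20% loss leaves 200 (power 0.94), 40% leaves 150 (0.86) and 50% leaves 125 (0.79). The margin down to 128 is 1 − 128/250 = 48.8%. Power is not the problem.

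**4. Bias from losses.** The listed covariates do not include the baseline outcome. With two time points the group-by-time test is therefore a contrast of mean changes. If a fraction p leaves an arm, and stayers and leavers differ in mean change by D, the stayers' mean differs from the full arm's mean by p × D. With the same D in both arms,

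bias = (p_AMT − p_control) × D.

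D is a difference in *change*. A stable difference in *level* cancels: with 30% versus 10% loss and a level difference of 0.5 SD, the arms shift by 0.20 × 0.5 = 0.10 SD before and by 0.10 SD after, and 0.10 − 0.10 = 0.

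Illustration, with p and D assumed and D on the same SD scale as d = 0.5:

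| Loss AMT / control | D = 0.2 | D = 0.5 | Share of d = 0.5 |
|---|---|---|---|
| 10% / 10% | 0 | 0 | 0 |
| 20% / 10% | 0.02 | 0.05 | 4% to 10% |
| 30% / 10% | 0.04 | 0.10 | 8% to 20% |
| 10% / 30% | −0.04 | −0.10 | 8% to 20%, opposite sign |

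**5. Bias from a shifted baseline.** The contrast is (post − pre) in AMT minus (post − pre) in control. If knowing the arm moves the AMT baseline by s relative to control and leaves the post value alone, the contrast moves by −s. An assumed s of 0.1 SD therefore moves it by the full 0.1 SD. The documents give no value for s.

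**The case against.** The strongest reply is that the article does not state the full sequence. The adverb in the allocation sentence attaches to tabulating the data, and both assignment and reconsent sit at the end of session 1. Matching people to one another also suggests waiting for a pool of completers. This stands: that reconsent follows assignment is an inference.

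A reader might infer that participants know their arm when asked to reconsent or when making the baseline recording. No sentence says so, and the timing of disclosure is a detail that an article can leave to the full protocol. If the arm is concealed until after the recording, neither arm-driven losses nor an anticipatory shift follows.

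Some text lowers the risk. Under Recruitment, the consent form describes both arms' procedures in advance. Under Session 8, controls are offered AMT afterwards. Both arms receive the same equipment, the baseline is device-recorded with identical tasks, and it precedes any training content, so training cannot have contaminated it.

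A reader might also take a difference in outcome level between decliners and stayers, multiply it by loss in one arm only, and call the result the bias. The planned pre-post contrast does not support that, as step 4 of the working shows.

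None of this changes the explicit part: equipment receipt and the H4-H6 baseline come after an assignment made from session 1 data.

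**Conclusion.** The point holds in a limited form, with moderate confidence. As written, allocation precedes equipment receipt and the entire H4-H6 baseline; it appears to precede reconsent as well. People lost at these steps leave the physiological analyses altogether. Whether the remaining comparison is biased depends on two things that the article does not give: whether the arm is known at these steps, and how loss differs between arms.

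Under the assumed inputs, loss bias runs from zero (equal loss and equal selection) to about 0.10 SD, a fifth of the planned effect, in either direction. A baseline shift tied to the arm would pass one for one into H4 to H6, but its size is unknown. Recruiting 250 protects power and does nothing about either bias. The documents do not show that such bias will occur. They show an order that permits it, when a safer order is available within the same procedures.

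**What to change.** Generate and reveal the assignment only after reconsent, confirmed equipment receipt and the common first part of session 2, using the session 1 scores already tabulated. Count everyone allocated at that point as randomised. Losses at reconsent and shipping then affect only generalisability, and every randomised person has a physiological baseline recorded before the arm is known.

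Reconcile this with the cluster randomised description in the Abstract and the Design section. If whole groups are in fact allocated, the group's arm should stay concealed until its members have completed the baseline recording.

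If the present order must be kept, state when the arm is disclosed, report losses by arm from assignment onward, and keep all assigned participants in the denominator. This is second best, because it documents the losses without preventing them.

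**Cost.** The sample size is unchanged and no extra equipment is needed, since both arms receive it already. The real cost lies in the matching. It must either run sequentially as people reach that point, for example by minimisation built into the learning platform, or wait until the cohort has finished the recording. Waiting would mean that AMT participants could not carry on in the same sitting, as session 2 now has them do. Matching would still rest on session 1 scores, because the HRV data stay on the device until it is mailed back.

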##### Session 2: Baseline Physiological Assessment and Introduction to AMT (40-60 Minutes)

All participants will be taught via web-based video modules how to apply the wearable HR monitor and configure the HRVBF app. The wearable HR monitor will automatically record date and time-stamped physiological data upon contact with the skin via the chest band and will communicate with the HRVBF app via Bluetooth. All HRV data will be stored locally on the HRVBF app and study device, which will be mailed back to the research team at the end of the study period. In the first part of this session, both experimental and control participants will provide baseline resting HRV and RSA data that will be recorded while participants engage in a 7-minute neutral activity (eg, listening to prerecorded sounds) that does not stimulate arousal or relaxation ([name], unpublished data, 2019). To assess recovery from an acute stressor, participants will perform web-based versions of the Paced Auditory Serial Addition Test (PASAT) [87] and the emotional Stroop task [88], both of which have been shown to induce significant sympathetic arousal but do not simulate traumatic material [28].

Following these baseline physiological assessments, participants in the experimental group will continue with the rest of their session (15-20 min) and begin the AMT intervention. Participants in the control group will not have any programming until session 8 (postintervention assessment).

##### AMT Intervention Sessions 3-7 (45-60 Minutes Each)

These sessions will be completed by participants in the experimental group only. The content of each AMT session will be modified from the Lehrer et al [30] HRVBF protocol and informed by practitioner, knowledge user, and stakeholder-informed design workshops to adhere to iKT principles and fit a web-based format [42]. Participants will use the HRVBF app linked via Bluetooth to their HR monitor to engage in paced breathing exercises, view their RSA progress and live HRVBF data, engage with psychoeducational content on the LMS, and complete their homework assignments (ie, paced breathing practice at least twice a day as per protocol) [30]. Participants will also view short video lectures, text, and educational content, and engage in practical exercises during each session. Participants will receive weekly emails with practice reminders and links to useful resources, including links to YouTube videos of their preferred breathing pace. Participants will learn about meta-cognitive and coping skills as they can help mitigate stress in operational, organizational, and personal contexts to foster holistic resilience and well-being.

##### Session 8: Postintervention Assessment (2 Hours)

All participants will receive an email reminder 1 week before the final session, which will be completed by both experimental and control participants. It will begin by obtaining objective physiological measures at rest, including HRV (7-minute neutral task), RSA (paced breathing), and recovery from acute stress (PASAT and Stroop tasks). Next, participants will complete the same self-reported questionnaires as in session 1 to assess changes in self-reported PTSI, resilience and well-being, occupational and operational stress exposure, and sex and gender-relevant data (see hypotheses). Participants in the control group will be asked if they would like to complete the AMT intervention. If so, they will be provided access to sessions 3 to 7 and will be asked to complete a second postintervention assessment (session 8) after completing the AMT intervention. Incentive payments will be processed as participants drop out or complete study assessments.

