### Biological Resilience Training: Heart Rate Variability Biofeedback

Research reveals a connection between respiration, arousal, and emotional control, such that how a person breathes sends signals to regions in the brainstem and forebrain that modulate arousal [28]. For example, periods of slow breathing are associated with SNS suppression and PNS stimulation, which may underlie the anxiety- and stress-reducing effects of RSA [28]. For nearly 3 decades, Lehrer and Gevirtz [21] have pioneered and refined a cardiorespiratory intervention called heart rate variability biofeedback (HRVBF). During HRVBF, a person is shown visual feedback of their beat-by-beat HR data while engaging in slow breathing with the goal of maximizing RSA. For clinically effective treatment, it is not sufficient to simply instruct a person to breathe slowly. Rather, HRVBF technology is required to identify the precise breathing rate for maximizing individual RSA and to condition this rate through training [29,30].

In collaboration with expert police practitioners as well as medical and academic experts in psychophysiological risk and resilience, the lead author developed the International Performance Resilience and Efficiency Program (iPREP), an in-person resilience program that improves occupational health and performance by addressing the unique acute and chronic stressors faced by police [31-33]. This program has been refined across 6 grant-funded multimethod studies with over 300 police participants measuring objective psychophysiological and behavioral data [31-40]. The components of the currently proposed intervention are based upon the same core scientific principles and validated intervention methods as iPREP, including mental health awareness and support [2] and psychophysiological techniques (ie, HRVBF) to promote resilience by conditioning adaptive HRV, RSA, and HR functioning [30,41,42]. Research has shown that the autonomic modulation techniques instructed during iPREP result in significant, long-term reductions in occupational errors and improvements in officers’ ability to recover quickly from acutely stressful events when completed during scenario-based, in-person training [31-33].

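### Paced breathing is listed ahead of the stress tasks at session 8 but not at session 2, so the two stress-recovery readings for H6 may not be taken under like conditions

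*Protocol article*

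**What the plan says.** Session 2 (Protocol article, Baseline Physiological Assessment and Introduction to AMT) has both arms provide "baseline resting HRV and RSA data that will be recorded while participants engage in a 7-minute neutral activity", an activity chosen as one "that does not stimulate arousal or relaxation". The PASAT and the emotional Stroop task follow. No paced breathing is named before them, and the experimental arm starts AMT only after these baseline measurements.

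Session 8 (Postintervention Assessment) opens with physiological measures, "including HRV (7-minute neutral task), RSA (paced breathing), and recovery from acute stress (PASAT and Stroop tasks". This session is one "which will be completed by both experimental and control participants", so the waitlist arm also does the paced breathing.

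Three other places bear on the point:

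- The background section on HRV biofeedback says that "periods of slow breathing are associated with SNS suppression and PNS stimulation".
- The description of sessions 3 to 7 gives the AMT arm "paced breathing practice at least twice a day as per protocol".
- Hypotheses, Outcomes and the analysis section word H6 as an improvement after AMT, score it by RMSSD after the stress tasks, and analyse it by pre-post repeated measures ANCOVA. The article names no group-by-time term for it.

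**The concern.** H6 compares recovery from the same stressors before and after the programme, so what precedes the stressors should be the same on both occasions. The plan shows that it cares about the preceding state, because the baseline activity was picked to be neither arousing nor relaxing. At follow-up, as listed, a spell of the active technique comes between that neutral recording and the stressors.

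By the article's own account slow breathing shifts autonomic balance towards the parasympathetic side, and RMSSD is an HRV measure that such a shift could raise. Part of a higher post-task RMSSD at session 8 could then reflect breathing done shortly before, and not a change in how officers recover. Once main-trial data are collected under unlike conditions, no analysis can fully separate the two.

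**Working it through.** **The plan's own figure.** The only design figure is the minimum total of 128 (f = 0.25, α = 0.05, power 0.80, two groups, two measures; Recruitment section). A noncentral F with λ = f²N = 0.0625 × 128 = 8 on 1 and 126 df gives power 0.801, so 128 reproduces. The point does not depend on it.

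**The two sessions side by side.**

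| | Session 2 | Session 8 (listed order) |
|---|---|---|
| First | Neutral 7-minute activity (HRV and RSA) | Neutral 7-minute task (HRV) |
| Between | Nothing named | Paced breathing (RSA) |
| Then | PASAT, emotional Stroop | PASAT, Stroop |
| Who | Both arms | Both arms |

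**How far an acute effect could matter.** The documents give neither the size of any carry-over nor the pre-post correlation ρ of RMSSD, so both are assumed. Assume also no true effect of AMT on recovery, a two-sided 5% test, and n = 125 per arm (about 250 planned, half in each arm). In units of the single-occasion SD, the SD of a change score is √(2(1 − ρ)), which is 1 at ρ = 0.5.

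- Pre-post test within the AMT arm, carry-over c: noncentrality = c√n / √(2(1 − ρ)). For c = 0.2 and ρ = 0.5 this is 0.2 × 11.18 = 2.24.
- Group-by-time test, carry-over larger by d in the AMT arm: noncentrality = d / [√(2(1 − ρ)) × √(2/n)]. For d = 0.2 and ρ = 0.5 this is 0.2 / 0.1265 = 1.58.

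Noncentral t distributions (124 and 248 df) then give these probabilities of a significant result, with ρ = 0.5:

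| Assumed carry-over (SD) | 0.1 | 0.2 | 0.3 |
|---|---|---|---|
| Pre-post within AMT arm (c) | 20% | 60% | 91% |
| Group by time, carry-over equal in both arms (c) | 5% | 5% | 5% |
| Group by time, carry-over larger in AMT arm by d | 12% | 35% | 66% |

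**Range.**

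- At 0.2 SD, moving ρ from 0.3 to 0.7 moves the pre-post figure from 47% to 82% and the differential group-by-time figure from 27% to 53%.
- With 64 per arm (the stated minimum) and ρ = 0.5, the differential group-by-time figures fall to 9%, 20% and 39%.

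**The case against.** Four objections have weight.

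**The order is inferred.** Session 8 gives a list, not a schedule. The list runs in the order of H4, H5 and H6, so it may follow the numbering of the outcomes. The article states no interval or washout, and a condensed article may leave block order to the full protocol. This stands: the point holds only if the list is the running order. Still, nothing in the text prevents that order, and the list matches the session 2 sequence of a neutral recording followed by the stressors.

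**Controls do the same breathing.** This also stands. A shared effect cancels in the randomised contrast, which stays at 5%. Only a difference between the arms biases it.

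**The duration is unknown.** Two tasks described as inducing sympathetic arousal come between the breathing and the recovery reading, and the article does not say how long the effect of slow breathing lasts. It may have faded by then.

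**The point may be only a consequence of the RSA mismatch.** RSA is recorded in the neutral activity at session 2 and under paced breathing at session 8, which affects H5 more directly. If session 8 went back to the neutral task, this concern would vanish too. If instead paced breathing were added at session 2, H5 would be put right, but breathing would still precede the stressor. H6 is therefore protected by some ways of resolving the mismatch and not by others, which is why it needs its own sentence.

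A reader might also infer that carry-over must be larger in the AMT arm, because the background says that merely instructing slow breathing is not enough. That remark concerns clinically effective treatment, not an effect lasting minutes. Twice-daily practice makes a larger effect plausible but does not establish it.

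**Conclusion.** The two session descriptions differ, and the difference bears on H6. If session 8 runs as listed, an acute effect of paced breathing is a rival explanation for any pre-post gain in recovery RMSSD, in either arm. The AMT-versus-waitlist contrast is affected only by differential carry-over. The 12%, 35% and 66% for 0.1, 0.2 and 0.3 SD are an illustration, not an estimate: they rest on an assumed differential, an assumed correlation of 0.5, all 250 officers analysed, and no allowance for attrition or clustering. With no differential the figure is 5%.

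A reader might go further and infer that a positive H6 could not be read as better recovery at all. The documents do not support that. The order is not stated outright, the waitlist arm removes the shared part, and neither the size nor the persistence of the effect is given.

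**What to change.** Reconcile the descriptions of sessions 2 and 8, and state one identical block order for both:

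1. The neutral 7-minute recording.
2. PASAT and Stroop, with the recovery recording.
3. Any paced-breathing RSA recording, last.

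An equally good alternative is to leave paced breathing out of the assessment and record RSA in the neutral task at both sessions. In either case, name the group-by-time contrast as the test of H6, so that anything common to both arms cancels.

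The cost is a reorder of modules on the web platform and a sentence in the protocol. It is cheapest before the main cohorts begin: the article reports 7 pilot participants registered as of April 2023 and intends to refine procedures after the pilot. If paced breathing is kept, RSA is recorded after the stress tasks, which is a small downside, though equal in both arms and at both sessions. No change to the homework practice is needed or proposed, since that belongs to the intervention.

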#### Objective Biological Indicators of PTSI Symptoms and Resilience

The following 4 hypotheses were proposed:

H4: Resting HRV will significantly increase following the completion of the AMT intervention.H5: RSA will significantly increase following the completion of the AMT intervention.H6: Recovery from acute stress will significantly improve following the completion of the AMT intervention.H7: Based on inconsistencies in the extant literature, we will conduct exploratory analyses of any potential sex and gender differences in HRV, RSA, and acute stress recovery at baseline and postintervention assessments.

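### Baseline RSA comes from a neutral task and session 8 RSA from paced breathing, so the H5 pre-post comparison mixes a change of task with any effect of AMT

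*Protocol article*

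**What the plan says.** All references are to the protocol article.

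- **Session 2 (Baseline Physiological Assessment):** both arms provide "baseline resting HRV and RSA data that will be recorded while participants engage in a 7-minute neutral activity", a task described as one "that does not stimulate arousal or relaxation". The PASAT and emotional Stroop follow. The AMT arm then starts training, while for controls: "Participants in the control group will not have any programming until session 8 (postintervention assessment".
- **Session 8 (Postintervention Assessment):** this session, "which will be completed by both experimental and control participants", starts with physiological measures described as taken at rest, listed as "HRV (7-minute neutral task), RSA (paced breathing), and recovery from acute stress (PASAT and Stroop tasks". The neutral task is now tied to HRV only.
- **Hypotheses (objective biological indicators), H5:** "RSA will significantly increase following the completion of the AMT intervention". No comparison with controls is named.
- **Outcomes:** RSA is scored as power at the respiratory frequency. No recording task is named.
- **Data Security and Analyses:** H4, H5 and H6 are each to be analysed pre-post by repeated measures ANCOVA with demographic covariates. A group-by-time term is not mentioned.
- **Biological Resilience Training:** HRV biofeedback is described as "engaging in slow breathing with the goal of maximizing RSA".

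**The concern.** A change score is interpretable only if the same quantity is measured under the same condition at both visits. Here the condition changes between visits. By the article's own account, slow breathing is the manoeuvre used to raise RSA. RSA is also scored at the respiratory frequency, so a task that sets respiration acts directly on the metric. The session 8 text still calls the paced-breathing value a resting measure, which hides the switch.

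Two things are at stake:

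1. A rise from session 2 to session 8 could be produced by the task alone, with no change in resting RSA.
2. The comparison between arms could reflect skill at a breathing exercise that one arm has practised at least twice a day and the other has not been taught.

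H5 is one of three non-exploratory physiological hypotheses (H4 to H6), and RSA is a named pre-post outcome in the abstract.

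**Working it through.** **The plan's own figure.** The only nearby number is the minimum total of 128 in Recruitment (f = 0.25, alpha 0.05, power 0.80, 2 groups, 2 repeated measures). It reproduces as a two-group comparison with no gain from repeated measures: noncentrality 128 × 0.25² = 8, df 1 and 126, power 0.801. The present point does not rest on it. It supplies 128/2 = 64 per arm as one case, and the planned total of about 250 supplies 125 per arm as the other.

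**Conditions side by side.**

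| | Session 2 | Session 8 |
|---|---|---|
| Resting HRV | neutral task | neutral task |
| RSA | neutral task | paced breathing |
| Paced-breathing practice beforehand, AMT arm | none described | weeks of training |
| Paced-breathing practice beforehand, controls | none | none |

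No paced-breathing baseline is described for both arms.

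**Test of pre-post change in one arm.** Assumptions: n = 125, equal SD at both visits, correlation r = 0.6, true AMT effect zero, acute task shift s in SD units.

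- SE of the mean change = sqrt(2(1 − r)/n) = sqrt(2 × 0.4/125) = 0.080.
- Probability of significance = P(|Z + s/SE| > 1.96).
- s = 0.1: s/SE = 1.25, probability 0.24.
- s = 0.2: s/SE = 2.50, probability 0.705.
- s = 0.3: s/SE = 3.75, probability 0.96.

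**Simulation of both arms.** Assumptions: r = 0.5, true AMT effect zero, the same task shift in both arms, participants independent (clustering ignored), 2,000 trials per case. The first two result columns count significant rises only.

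| Per arm | Shift (SD) | AMT-arm rise | Time main effect | Group × time |
|---|---|---|---|---|
| 64 | 0 | 2.6% | 2.3% | 5.2% |
| 64 | 0.25 | 49% | 81% | 4.8% |
| 64 | 0.5 | 98% | 100% | 5.1% |
| 125 | 0.25 | 79% | 97% | 4.9% |
| 125 | 0.5 | 100% | 100% | 4.5% |

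A common shift drives the two pre-post tests and leaves group-by-time at its nominal level.

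**Unequal response to paced breathing.** Suppose practice gives the AMT arm an extra u SD on the paced task, with resting RSA unchanged. The SE of the difference in change is sqrt(4(1 − r)/n). With r = 0.5 this is sqrt(2/64) = 0.177 or sqrt(2/125) = 0.126.

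- u = 0.25: group-by-time is significant in about 29% of trials (64 per arm) or 50% (125 per arm).
- u = 0.5: about 80% or 98%.

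The simulation gives the same values to within sampling error, whatever the size of the common shift.

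**The case against.** The strongest reply is that this is a parallel randomised design, sized with two groups and two measures, and that controls sit the same session 8. A task effect shared by both arms then cancels in the comparison of change. The only analysis in which a time main effect is spelled out is the weekly one during training, not H5. This stands. A reader might infer that H5 is bound to be confirmed by the change of task, or that controls will also show a rise. The documents do not support either inference: the test for H5 is not fixed as a one-arm comparison, no figure is given for the acute rise, and the pace used at session 8 is not stated. The 0.24, 0.705 and 0.96 above describe a one-arm test only.

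The cancellation does not settle the matter. It needs both arms to respond equally to paced breathing, and the article gives reason to doubt that. It says that telling someone to breathe slowly is not enough for effective treatment, and that the individual rate must be identified and conditioned through training. Only the AMT arm receives that before session 8. Randomisation would still support a claim about RSA during paced breathing, but not one about RSA at rest.

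It can also be said that Outcomes names no task and that an article condenses its full protocol. But this is not an omission: the article states both recording conditions, and they differ.

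Finally, a reader might infer that paced breathing at session 8 carries over into the PASAT and Stroop recovery measure (H6). That rests on the order of a list introduced as examples of the measures. No sequence is stated, so the point is conditional.

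**Conclusion.** The point holds in a limited form. The session 2 and session 8 sections name different conditions for RSA, and a change score taken across them cannot be attributed to AMT. If H5 is judged on the AMT arm's change or on the time main effect, modest assumed shifts are enough for a false positive: 0.24 to 0.96 for 0.1 to 0.3 SD with 125 in the arm and r = 0.6. If it is judged on group-by-time, a common shift does no harm (error about 5%). A practice advantage of 0.25 to 0.5 SD could still produce a significant contrast in about 29% to 80% of trials at 64 per arm, or 50% to 98% at 125, with no change at rest. All shifts, practice gains and correlations here are assumptions, so the actual size is unknown. The 7-minute neutral recording is already planned at both sessions, so the defect can be fully repaired before analysis.

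**What to change.** Reconcile the session 2 and session 8 sections, and carry the result into Outcomes and Data Security and Analyses:

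1. Define the H5 outcome as RSA from the 7-minute neutral recording at both session 2 and session 8, in both arms.
2. State that H5 is tested by the group-by-time term, or by session 8 RSA adjusted for the same-task baseline.
3. Report session 8 paced-breathing RSA separately, as a measure of skill or fidelity, and do not describe it as resting.
4. If paced breathing would in fact come before the PASAT and Stroop at session 8, record it after them, so that the H6 sequence matches session 2.

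The alternative of adding a paced-breathing recording for both arms at session 2 would give a same-task baseline. It needs a new recording, however, and the between-arm contrast would still include practice.

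**Cost:** small edits to the wording and possibly to the order of the web modules, with no new data. The downside is that H5 then speaks to resting RSA only; any gain seen only during paced breathing moves to the separate measure.
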